## Abstract

**Background:**

Approximately 30% of HIV-1-infected patients receiving antiretroviral therapy who achieve virologic control have unsatisfactory immune reconstitution, with CD4+ T-cell counts persistently below 350 cells/μL. These patients are at elevated risk for clinical progression to AIDS and non-AIDS events. CD4+ T-cell depletion following infection and persistent immune activation can partially explain this low CD4+ T-cell recovery. Recent data suggest a link between the tryptophan oxidation pathway, immune activation and HIV disease progression based on overstimulation of the tryptophan oxidation pathway by HIV antigens and by interferon-gamma. This overstimulation reduces levels of circulating tryptophan, resulting in inflammation which has been implicated in the development of neurocognitive dysfunction. Niacin (vitamin B3) is able to control the excess tryptophan oxidation, correcting tryptophan depletion, and therefore represents an interesting strategy to improve CD4 recovery.

We aim to design a crossover proof-of-concept study to assess supplementation with an extended-release form of niacin (Niaspan FCT™) in combination with antiretroviral therapy, compared to antiretroviral therapy alone, on T-cell immune activation as defined by changes in the percentage of CD8+ CD38+ HLA-DR+ T-cells.

**Methods/Design:**

This randomized, open-label, interventional crossover study with an immediate versus deferred use of Niaspan FCT for 24 weeks will assess its ability to reduce immune activation and thus increase CD4 recovery in 20 HIV-infected individuals with suboptimal immune responses despite sustained virologic suppression. A substudy evaluating neurocognitive function will also be conducted.

**Discussion:**

This randomized trial will provide an opportunity to evaluate the potential benefit of oral extended-release niacin, a drug that can indirectly increase tryptophan, to reduce immune activation and in turn increase CD4+ T-cell recovery. The study will also allow for the evaluation of the impact of Niaspan FCT on neurocognitive function in HIV-infected individuals with suboptimal immune responses despite sustained virologic suppression.

**Trial registration:**

This study was registered with ClinicalTrials.gov on 17 December 2013 (registration number: NCT02018965).

**Electronic supplementary material:**

The online version of this article (doi:10.1186/1745-6215-15-390) contains supplementary material, which is available to authorized users.

## Background

Approximately 30% of antiretroviral therapy (ART)-treated patients who achieve virologic control have an unsatisfactory immune reconstitution, with CD4+ T-cell counts persistently below 350 cells/μL [1, 2]. These patients remain at an elevated risk for clinical progression to both AIDS and non-AIDS events [1, 3–5]. Depending on the definition, it is estimated that between 5 and 20% of patients starting ART can be considered as immunological non-responders. These individuals have suboptimal CD4+ T-cell recovery despite having complete suppression of their plasma viral load [6, 7]. Accumulating data suggest that CD4+ T-cell depletion following infection, as well as persistent immune activation, can partially explain this low and/or slow CD4+ T-cell recovery [1, 8, 9]. Indeed, in patients receiving effective ART, the persistence of enhanced T-cell activation (defined by co-expression of CD38 and HLA-DR on CD8+ T-cells) and elevated plasma levels of markers of inflammation, such as interleukin (IL)-6, C-reactive protein (CRP) and D-dimers, represent factors associated with low CD4+ T-cell recovery [10–12]. In addition, persistent immune activation leads to a chronic inflammatory state that is associated with an increased risk of the non-opportunistic complications that are observed in ART-treated individuals, such as cardiovascular, renal and hepatic events [13, 14].

Recent data suggest a link between the tryptophan (Trp) oxidation (TrpOx) pathway (also known as the Trp catabolism pathway), immune activation and HIV disease progression [15, 16]. Indoleamine 2,3-dioxygenase (IDO) expressed by dendritic cells and macrophages catabolizes the essential amino acid Trp into an immunosuppressive metabolite kynurenine (Kyn) that limits immune responses [17]. It has been reported that IDO mediates the loss of IL-17-secreting (Th17) cells that enhance host defenses against microbial pathogens, mainly at mucosal barrier sites [15]. As a result of the disturbance in the balance between Th17 and immunosuppressive T-regulatory (Treg) cells, there is a breakdown of the mucosal barrier. This breakdown causes increased levels of circulating microbial products, such as lipopolysaccharides (LPS), which sustain chronic immune activation [18, 19].

Trp is an essential amino acid required for the biosynthesis of proteins, serotonin and niacin, which is a vitamin B3 compound [20]. Both HIV antigens and interferon-gamma (IFN-γ) can overstimulate the TrpOx pathway by activating IDO, resulting in Trp catabolism into Kyn [15]. As IDO is the rate-limiting enzyme in the metabolism of Trp along the Kyn pathway, circulating levels of Trp are reduced in HIV-infected patients despite adequate dietary intake [16]. Following Trp catabolism into Kyn under the influence of IDO, there is an additional catabolic pathway in which the metabolites contribute to an imbalance between neuroprotective and neurotoxic metabolites in the Kyn pathway [21, 22]. This occurs when Kyn is further catabolized by the enzyme kynurenine-3-mono-oxygenase into 3-hydroxy-Kyn (3-OHK) and the N-methyl-D - aspartate (NMDA) receptor agonist quinolinic acid. 3-OHK causes neuronal apoptosis while quinolinic acid causes excitotoxic neurodegenerative changes. Moreover, quinolinic acid has pro-inflammatory properties [23], further stimulating IDO and thus aggravating the inflammatory response and Trp degradation. However, Kyn can also be catabolized into kynurenic acid, which is an NMDA receptor antagonist and is protective against the excitotoxic action of quinolinic acid [24]. Evidence linking the Kyn pathway and cognitive dysfunction has been recently reviewed by Davies *et al*. [21]; both direct and indirect evidence supports its role in Alzheimer’s disease as well as in HIV-associated neurocognitive disorders (HANDs). Thus, it is plausible that modifying Trp metabolism along the Kyn pathway may improve HANDs.

*In vitro* data has shown that Trp depletion can significantly impede T-cell reconstitution by reducing both CD4+ T-cell proliferation and survival [25, 26]. ART is able to partially decrease immune activation through viral load suppression while normalizing Trp plasma levels and decreasing Trp catabolism into Kyn [27–29]. Ongoing IDO activation also appears to contribute significantly to the development of several symptoms known to deteriorate a patient’s quality of life (QoL). These include the neuropsychiatric symptoms of fatigue, anemia and weight loss experienced by HIV and cancer patients [30, 31].

Collectively, these data strongly suggest that declining Trp levels are associated with immunosuppression, mood disturbances and cognitive impairment, thereby leading to the hypothesis that oral Trp supplementation should contribute to improved immune responses and cognitive function. However, in clinical studies, direct Trp supplementation in the presence of ongoing immune activation was associated with increased risks of neurotoxic problems, oxidative stress and possibly the development of eosinophilia-myalgia syndrome, a rare and deadly flu-like condition [32, 33].

An indirect way to increase Trp levels while minimizing the side effects of direct Trp supplementation is to provide exogenous niacin, a key player in the TrpOx pathway. Niacin, also known as vitamin B3, nicotinic acid and vitamin PP, is able to control excess Trp oxidation by a process of reverse inhibition [34]. It has been shown that exogenous niacin supplementation in the form of nicotinamide, the major circulating form of niacin, is able to correct Trp depletion and improve CD4+ T-cell recovery [35, 36]. Improvements in cognitive test scores and overall function have been reported in European trials of pharmacological preparations that include niacin [37].

In one small study, four ART-naïve HIV-infected individuals were treated with a supplement of 3,000 mg/day of immediate-release (IR) niacin for two months. The treatment was not associated with the usual side effects such as flushing (described as warmth), redness, itching and/or tingling, and resulted in a 40% increase in plasma Trp levels and clinical benefits [36]. However, further studies on the effectiveness of niacin to increase Trp levels are needed to confirm these results.

Niaspan FCT™ is an extended-release (ER), oral form of niacin that is dosed once each night when cholesterol synthesis and fatty acid mobilization are at their peak. Niaspan FCT has intermediate-release characteristics and is thus designed to minimize both liver enzyme elevation and flushing [38].

Niacin is the most effective agent at raising high-density lipoprotein cholesterol levels, either as a monotherapy or in combination with other agents, despite the fact that it has not consistently shown improved patient outcomes [39]. However, it has been recently shown that in patients with atherosclerotic cardiovascular disease and low-density lipoprotein cholesterol levels, there was no incremental clinical benefit from the addition of niacin to statin therapy, despite significant improvements in high-density lipoprotein cholesterol and triglyceride levels. We will, therefore, also assess the ability of Niaspan FCT to improve cholesterol and triglyceride levels [40].

Since the beginning of the AIDS epidemic, HANDs have been commonly observed in individuals in the advanced stage of the disease [21]. More recently, age, cerebrovascular diseases and the Kyn pathway and immune activation have also been suggested to be involved in HANDs [21, 22, 41]. Low nadir CD4 cell count and low CD4 recovery have also been reported in many studies as risk factors for prevalent neurocognitive impairments [42, 43].

Schroecksnadel *et al*. reported that enhanced Trp degradation was associated with impaired QoL in patients with cancer [30]. Collectively, these data strongly suggest that enhanced Trp degradation by persistent immune activation may provide an explanation for HANDs in HIV-infected patients despite treatment with ART [21, 22].

Given that ER niacin can indirectly increase Trp levels, we seek to further assess the effects of ER niacin on neurocognitive functions and QoL among HIV-infected individuals who choose to participate in a substudy of this clinical trial.

This pilot crossover study will be conducted to examine the ability of ER niacin to reduce immune activation, which may in turn increase CD4 recovery in HIV-infected individuals with suboptimal immune responses despite sustained virologic suppression. The main hypothesis to be tested is that ER niacin co-administration with ART will be associated with decreased T-cell activation as determined by changes in the percentage of activated CD8+ CD38+ HLA-DR+ T-cells. If so, during administration of ER niacin, participants should experience a time-dependent decrease in T-cell activation, and such a decrease may reverse after ER niacin is discontinued. We will also examine the effects of ER niacin on cognition. To this end, we will assess the neurocognitive function and QoL in participants using standardized neuropsychological (NP) tests and questionnaires.

## Methods/Design

### Study design

This is a randomized, open-label, interventional crossover study (the Canadian HIV Trials Network (CTN) number PT006) with an immediate versus deferred use of ER niacin for 24 weeks to assess the ability of oral ER niacin to reduce immune activation (as determined by the percentage of activated CD8+ CD38+ HLA-DR+ T-cells), which may in turn increase CD4+ T-cell recovery in HIV-infected individuals who achieve suboptimal immune responses despite sustained virologic suppression. Participants will continue to take their ART treatment as prescribed throughout the study. The study design is shown in Figure 1.

**Figure 1 Fig1:**
[figure not shown]
**Study design.** Arm 1: ER niacin administration begins at week 0 and ends at week 24 (defined as ‘immediate use’ arm). Arm 2: ER niacin administration begins after the week 24 visit and ends at week 48 (defined as ‘deferred use’ arm). ART, Antiretroviral therapy; ER, extended-release.

### Setting

Participants will be recruited at the Chronic Viral Illness Service, Montreal Chest Institute of the McGill University Health Centre (MUHC), one of the largest hospital-based centers in Montreal, Quebec, Canada, and at the Clinique médicale l’Actuel, the largest private medical centre in Montreal.

### Recruitment and enrollment

Prior to physical contact with any patient by the study staff, the HIV specialist at each HIV clinic will conduct chart reviews of prospective HIV-positive participants ahead of their scheduled clinic visits to determine which patients successfully treated with ART did not complete immune restoration. Based on this information, the research nurse and/or the referring HIV specialist will approach potential trial participants upon arrival at the clinics. At this time, the trial staff will inform the patient about the trial and invite him or her for eligibility screening and possible enrolment into the trial. Prior to enrolment, trial participation eligibility will be documented, and written informed consent will be obtained from eligible patients by the treating physician (Please see Additional file 1). Individuals who wish to discuss their participation in the study with their treating physician and/or with their family are given an opportunity to do so and may enrol at their next scheduled clinic visit. After enrolment, all participants will be followed during this trial by the principal investigator at the Chronic Viral Illness Service. In cases where the patient lacks capacity, a legal representative will provide consent.

#### Inclusion criteria

Eligible participants must meet all of the following criteria within four weeks prior to the week 0 (baseline) visit to be considered eligible for entry into the study: 1) documented HIV infection by western blot, enzyme immunoassays or viral load assay; 2) aged 21 years or older; 3) viral load <50 copies/mL for the last three months; 4) CD4+ T-cell count ≤350 cells/μL; and 5) on stable ART (ART unchanged for treatment failure (rebound in viral load)) for more than 12 months.

#### Exclusion criteria

Subjects who meet any of the following criteria will be excluded: 1) prior history of hypersensitivity reaction to niacin or any other component of the study drug; 2) prior history of flushing; 3) liver disease (including co-infection with hepatitis B or C virus) or unexplained persistent elevations of serum transaminases; 4) alanine aminotransferase (ALT) or aspartate aminotransferase (AST) or alkaline phosphatase >2.5 times the upper limit of normal (ULN); 5) active duodenal or gastric peptic ulcer; 6) active bleeding disorders; 7) history of gout; 8) active AIDS events in the last three months as determined by the treating physician; 9) unstable angina or acute phase myocardial infarction; 10) diabetic or potentially diabetic with hypercholesterolemia; 11) renal dysfunction; 12) co-enrollment in another study involving neurocognitive evaluation; or 13) pregnant or nursing or planning to become pregnant. Infection with syphilis, for which testing is done at screening, is not an exclusion criterion if the patient is treated; participants will be tested again at weeks 24 and 48.

### Study intervention

The study medication is ER niacin (Niaspan FCT; Sunovion Pharmaceuticals Canada Inc., Mississauga, Ontario, Canada) 500 and 1,000 mg ER film coated tablets (FCT) which will be taken at bedtime. The dose for this study is that recommended in the Niaspan FCT product monograph for the treatment of dyslipidemia [44]. ER niacin will be administered as outlined in Tables 1 and 2.

**Table 1 Tab1:** **Arm 1 study drug administration schedule**

	Weeks	Daily dose	Niaspan FCT dosage
Initial titration schedule	0 to 4	500 mg	One 500 mg tablet at bedtime
	5 to 8	1,000 mg	One 1,000 mg tablet or two 500 mg tablets at bedtime
	9 to 12	1,500 mg	One 1,000 mg tablet and one 500 mg tablet at bedtime
	13 to 24	2,000 mg	Two 1,000 mg tablets at bedtime

**Table 2 Tab2:** **Arm 2 study drug administration schedule**

	Weeks	Daily dose	Niaspan FCT dosage
Initial titration schedule	25* to 28	500 mg	One 500 mg tablet at bedtime
	29 to 32	1,000 mg	One 1,000 mg tablet or two 500 mg tablets at bedtime
	33 to 36	1,500 mg	One 1,000 mg tablet and one 500 mg tablet at bedtime
	37 to 48	2,000 mg	Two 1,000 mg tablets at bedtime

*Arm 2 extended-release niacin administration starts after the week 24 visit.

### Randomization

Once a participant is deemed eligible and has provided consent, they will be randomized to one of two treatment arms in a 1:1 ratio to receive the immediate or the deferred intervention with ER niacin. Prior to the initiation of the trial, a CTN staff member not directly associated with the implementation of the trial will use an SAS module (SAS Institute, Cary, North Carolina, United States) to generate sequential participant study identification numbers which will be loaded onto a webpage randomization system. The treatment groups will be: arm 1: ER niacin supplementation for 24 weeks followed by 24 weeks of ART alone, and arm 2: 24 weeks of ART alone followed by ER niacin supplementation for 24 weeks. When a participant is deemed eligible, the study coordinator signs onto the password-protected randomization webpage which issues the allocation. A transaction file records the study identification number, allocation and date and time of randomization.

Scheduled visits for arm 1 of this study will be screening (up to four weeks prior to treatment), week 0 (baseline), week 4, week 8, week 12, week 16, week 20, week 24, and week 48/final visit (or other if terminating early). Table 3 shows the arm 1 schedule of study events.

**Table 3 Tab3:** **Visit schedule, arm 1**

	Screening	Week 0	Week 4	Week 8	Week 12	Week 16	Week 20	Week 24	Week 48 (final visit)
Visit number	V1	V2	V3	V4	V5	V6	V7	V8	V9
Consent form	X								
Medical history	X								
Dietary survey		X							
Physical exam and vital signs	X	X	X	X	X	X	X	X	X
Adverse events		X	X	X	X	X	X	X	X
Hematology	X	X	X	X	X	X	X	X	X
Chemistry	X	X	X	X	X	X	X	X	X
Pregnancy test (women only)	X								
Hepatitis B and C tests	X								
ART review	X								
Syphilis test^1^	X							X	X
T-cell activation and inflammatory markers		X						X	X
HIV viral load^2^	X				X			X	X
Levels of tryptophan, niacin and its derivatives		X		X		X		X	X
ER niacin admin^3^		X	X	X	X	X	X	X	
Bays-Ballantyne questionnaire			X	X	X	X	X	X	
WHOQOL-HIV BREF, CES-D, POMS, HVLT-R™, and CANTAB™ tests^4^		X						X	X
SMAQ^5^		X			X			X	X

^1^If Syphilis test is positive at screening, participants will be retested at weeks 24 and 48.

^2^HIV viral load testing will be performed as indicated by treating physician.

^3^Participants will end ER niacin administration at the end of week 24.

^4^Neurocognitive assessments are optional; WHOQOL-HIV BREF, World Health Organization quality of life instrument in patients with HIV infection-brief; CES-D, Center for Epidemiologic Studies Depression Scale; POMS, Profile of Mood State; HVLT-R™, Hopkins Verbal Learning Test Revised; CANTAB, Cambridge Neuropsychological Test Automated Battery.

^5^SMAQ, Simple Medication Adherence Questionnaire.

Scheduled visits for arm 2 of this study will be screening (up to four weeks prior to study enrolment), week 0 (baseline), week 24, week 28, week 32, week 36, week 40, week 44 and week 48/final visit (or other if terminating early). Table 4 shows the arm 2 schedule of study events.

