**Table 4 Tab4:** **Visit schedule, arm 2**

	Screening	Week 0	Week 24	Week 28	Week 32	Week 36	Week 40	Week 44	Week 48 (final visit)
Visit number	V1	V2	V3	V4	V5	V6	V7	V8	V9
Consent form	X								
Medical history	X								
Dietary survey		X							
Physical exam and vital signs	X	X	X	X	X	X	X	X	X
Adverse events		X	X	X	X	X	X	X	X
Hematology	X	X	X	X	X	X	X	X	X
Chemistry	X	X	X	X	X	X	X	X	X
Pregnancy test (women only)	X		X						
Hepatitis B and C tests	X								
ART review	X								
Syphilis test^1^	X		X						X
T-cell activation and inflammatory markers		X	X						X
HIV viral load^2^	X		X			X			X
Levels of tryptophan, niacin and its derivatives		X	X		X		X		X
ER niacin admin^3^				X	X	X	X	X	X
Bays-Ballantyne questionnaire				X	X	X	X	X	X
WHOQOL-HIV BREF, CES-D, POMS, HVLT-R™, and CANTAB™ tests^4^		X	X						X
SMAQ^5^		X	X			X			X

^1^If syphilis test is positive at screening, participants will be retested at weeks 24 and 48.

^2^HIV viral load testing will be performed as indicated by treating physician.

^3^Participants will start ER niacin administration after their week 24 visit.

^4^Neurocognitive assessments are optional; WHOQOL-HIV BREF, World Health Organization quality of life instrument in patients with HIV infection-brief; CES-D, Center for Epidemiologic Studies Depression Scale; POMS, Profile of Mood State; HVLT-R™, Hopkins Verbal Learning Test Revised; CANTAB, Cambridge Neuropsychological Test Automated Battery.

^5^SMAQ, Simple Medication Adherence Questionnaire.

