### Measurements

At baseline, the following clinical information will be collected for all participants: age, education, ethnicity, handedness, communication skills (able to communicate in English and/or French adequately, first language), list of current psychoactive medication, dosage and date of treatment initiation, psychiatric disorders, duration of HIV infection, current ART regimen (duration in months), review of ART history, CD4+ T-cell count within the past three months, nadir CD4+ T-cell count, HIV plasma viral load within the past three months and any preexisting medical conditions, signs, or symptoms.

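### Arm 1's only scheduled pregnancy test may be up to four weeks old at the first niacin dose; a week 0 test would be a cheap, optional safety improvement

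*Protocol article*

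**What the plan says.** The Exclusion criteria section bars women who are "pregnant or nursing or planning to become pregnant" (criterion 13).

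For arm 1, Table 3 has a row headed "Pregnancy test (women only") with a single mark, in the screening column. The Randomization section places that visit as follows: "Scheduled visits for arm 1 of this study will be screening (up to four weeks prior to treatment"). The Figure 1 legend gives the start of dosing: "Arm 1: ER niacin administration begins at week 0 and ends at week 24". Table 3 repeats the physical exam, hematology and chemistry at week 0, but not the pregnancy test. Table 1 then raises the daily dose from 500 mg to 2,000 mg ("Two 1,000 mg tablets at bedtime" from week 13).

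For arm 2, Table 4 marks the pregnancy test at screening and again at week 24. Its footnote 3 adds: "Participants will start ER niacin administration after their week 24 visit".

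The Measurements section collects at baseline "any preexisting medical conditions, signs, or symptoms".

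**The concern.** An exclusion that protects a participant from the study drug is best confirmed close to the first dose. As the schedule is printed, a woman in arm 1 who conceives between screening and week 0 can begin niacin on an out-of-date negative result, although she then meets an exclusion criterion. The baseline history could reveal a pregnancy she knows about, but not one she has not yet recognised.

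What is at stake is a possible drug exposure in a very small number of women. The primary comparison, sample size and error rates are untouched.

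The article prints the full visit schedule with an explicit pregnancy-test row, and the week 0 cell in that row is empty. The point therefore concerns what the schedule states, not a detail that a condensed article leaves to a fuller document.

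**Working it through.** The plan gives no figure to reproduce here, so the check is a reading of the schedule followed by an illustration of size.

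**Age of the last test at first dose**

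| | Arm 1 (Table 3) | Arm 2 (Table 4) |
|---|---|---|
| Pregnancy tests scheduled | Screening | Screening, week 24 |
| First niacin dose | Week 0 | After the week 24 visit |
| Screening to first dose | 0 to 4 weeks | 24 to 28 weeks |
| Last test to first dose | 0 to 4 weeks (at most 4 × 7 = 28 days) | About 0 days |
| Last test to first dose, with a week 0 test in arm 1 | 0 days | Unchanged |

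Arm 1 has 1 test in 9 scheduled visits, and none in the 7 visits from week 0 to week 24. After its week 24 test, arm 2 also has none at weeks 28 to 48.

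**Illustration of size**

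With 20 participants randomized 1:1, about 10 are in arm 1. The document does not give the number of women or a pregnancy rate. I assume n = 1 to 5 women in arm 1 and a yearly pregnancy rate p = 1% to 10% among women not planning pregnancy.

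- Risk per woman over a full four-week window: w = 1 − (1 − p)^(4/52). For p = 1%, w = 0.077%. For p = 10%, w = 0.807%.
- Chance of at least one pregnancy among n women: 1 − (1 − w)^n.

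| n | p per year | Chance of at least one |
|---|---|---|
| 1 | 1% | 0.08% |
| 3 | 5% | 1.18% |
| 5 | 10% | 3.97% |

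These are chances that a pregnancy begins in the window, not that harm follows. They take the full four weeks for every woman, so they are upper values for each pair of assumptions.

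**How much of the exposure period the fix touches**

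From the earliest screening to the end of arm 1 dosing is 4 + 24 = 28 weeks. A week 0 test bears on at most 4 of these, or 4/28 = 14%.

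**The case against.** The strongest reply is that nothing here is an error. The inclusion criteria are assessed within four weeks before week 0, and in Table 3 the hepatitis tests and the review of antiretroviral therapy are also done at screening only. A screening-only pregnancy test fits that approach, and asking for a second one is a preference for a tighter standard. This stands, and it is why the point is optional.

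A reader might infer from the week 24 test in Table 4 that the two arms contradict each other. The documents do not support that. The arm 2 retest is explained by the 24 to 28 weeks since its screening, and both arms have a test within four weeks of first dose. What Table 4 does show is that testing at the visit from which dosing starts is feasible in this trial.

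A reader might also infer that a week 0 test closes the gap, or that it deals with the absence of tests during the 24 weeks of dosing. It does neither. A conception only days old can be missed at week 0, and a conception during dosing would go without a scheduled test in both arms, exactly as now.

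Three further points stand:

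- The article states no fetal risk for niacin, so the consequence of a few weeks' exposure cannot be sized from it.
- The probabilities above rest wholly on assumptions.
- Physical exams and active enquiry about adverse events at each clinic visit are partial safeguards, though they do not replace a test.

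Finally, the Trial status section reports a start in February 2012 and expects enrolment to be complete by November 2014, so a change helps only women in arm 1 who have not yet been dosed.

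**Conclusion.** The point holds as a minor, optional participant-safety improvement. Arm 1's last scheduled pregnancy test can be up to 28 days old at first dose, and a test at the existing week 0 visit would reduce that to 0 days. This follows directly from Table 3, the Randomization section and the Figure 1 legend, and needs no assumption.

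The benefit is very small: 0.08% to 4.0% across the assumed ranges, and about 1.2% for three women at 5% a year. Part of that would remain after the fix, because a test on the day cannot detect every early conception. There is no effect on the analysis. The case for acting rests on how little the change costs, not on the size of the risk.

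**What to change.** In Table 3, add a mark for the pregnancy test (women only) at week 0, and require the result to be seen before the first dose. The Study intervention section describes "ER film coated tablets (FCT) which will be taken at bedtime", so a same-day test at that visit gives a result in time.

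The cost is one inexpensive test per woman in arm 1, at a visit where hematology and chemistry are already done. The downside is that an occasional participant will not start niacin. Visit count, sample size, power and significance level do not change. Table 4 needs no change for this point.
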